## Abstract

(1) Background: We have previously shown that sputum rheology can discriminate between patients with COPD and other muco-obstructive lung diseases, and that it is correlated with mucin content and sputum eosinophilia. We now hypothesize that it could be a more-accurate guide than clinical evaluation for the prescription of azithromycin to prevent exacerbations of COPD and to reduce exposure to antibiotics; (2) Methods: “COPD CaRhe” is a multicentric, randomized, controlled trial comparing outcomes in two parallel arms (36 vs. 36 patients). Patients will be recruited in the university hospitals of Montpellier, Bordeaux, and Toulouse, in France, and they should have a diagnosis of COPD with frequent exacerbations (≥3/year). Enrollment will occur during a routine visit to a respiratory department, and follow-up visits will occur every 3 months for a period of 1 year. At each visit, a 3-month prescription of azithromycin will be provided to those patients who obtain a score of <70 on the Cough and Sputum Assessment Questionnaire (CASA-Q) or a critical stress score of σc > 39 on a rheological assessment of sputum, depending upon their randomization group. The primary outcome will be the number of exacerbations of COPD; (3) Discussion: By using sputum rheology, the COPD CaRhe study may provide clinicians with an objective biomarker to guide the prescription of azithromycin while reducing the cumulative exposure to macrolides.

## 1. Introduction

Chronic obstructive pulmonary disease (COPD) is a devastating and currently irreversible chronic disease that affects approximately 10–13% of the European population [1,2]. Its prevalence and incidence are increasing [3]. Chronic bronchitis (chronic cough and sputum) is a feature of COPD which is predictive of acute exacerbations of COPD (AECOPD) [4]. These events are part of the natural history of this disease and a marker of poor prognosis [5]. For instance, in France, more than 8% of patients hospitalized with acute AECOPD die during their stay [6]. Currently, therapeutic strategies aim to decrease their annual rate.

For a long time [7], several elements have been analyzed in sputum to determine the stable or exacerbated character of COPD, including its volume, its color, and its purulence. Sputum is classically attributed to excessive mucus production in the respiratory tract. This hyperproduction of mucus is now even thought to play a major role in distal airway (bronchiolar) obstruction, which is then complicated by emphysema [8]. While mucus production is a classic symptom of exacerbations, this symptom persists in the chronic form in slightly more than half of patients, with a rather negative significance, even if this remains controversial [4,9]. (Chronic bronchitis is defined by the presence of cough and sputum for 3 consecutive months over a period of at least 2 years.) This excess of mucus is responsible for chronic sputum that constitutes a considerable dimension of the burden carried by patients in this disease. However, at the moment, in France, there is no treatment reimbursed by health insurance that specifically targets this symptom, mostly due to lack of evidence or efficacy.

Multiple components vary in this sputum, and they are independent of the intrinsic quality and quantity of mucus [10] produced by the epithelium: microorganisms, epithelial cellular debris, polynuclear DNA, and other inflammatory cells. These changes are likely to modulate the rheology of the mucus [11]. Mucus is a complex, viscoelastic component consisting essentially of water, ions, and proteins, some of which (with the mucins MUC5AC and MUC5B being the most commonly represented) can modulate the biological and biophysical properties of mucus. Goblet cell hyperplasia and metaplasia would thus be the primum movens of chronic bronchitis [12,13]. This airway remodeling is partially explained by an increased production of certain cytokines (IL-4, IL-13, etc.) and mediators of epithelial or systemic origin [14]. The complexity of the pathophysiology of COPD is difficult to portray; nevertheless, it may be approached through the elaboration of biological network models that focus on cell proliferation, cell fate, or inflammation [15]. All of these processes are implied in the hyperproduction of mucus. Interestingly, azithromycin has been shown to decrease neutrophil chemotaxis in the lower respiratory tract [16], to improve the phagocytic capacity of alveolar macrophages [17], and to reduce some markers of systemic inflammation. However, equally convincingly, azithromycin has been shown to inhibit the hypersecretion of mucus by airway epithelial cells [18], which may explain why this macrolide engenders fewer exacerbations. Indeed, in clinical trials, the use of long-term azithromycin at a reduced-dosage regimen (either 250 mg/d or 500 mg/3 times per week) significantly reduced the annual rate of AECOPD, respectively, by 27% and 42% in two large, randomized, double-blind, controlled trials against placebo [19,20]. Moreover, it also proved efficient in improving the cough-specific health status of patients with COPD [21] and the Leicester Cough Questionnaire (LCQ) scores of patients with resistant cough [22]. As a result, azithromycin is now proposed in international and French guidelines as a therapeutic tool for the prevention of exacerbations, in addition to optimal standard management [23,24]. However, the pathophysiological link between azithromycin administration and the reduction of COPD exacerbations has not been established. As macrolides may cause infrequent, but significant, adverse effects (e.g., deafness; cardiac conduction disorders) and may increase microbial resistance, prescriptions of this type of molecule must be properly targeted. Nevertheless, the COPD patient population receiving azithromycin (or macrolides in general) is poorly defined and far from specifically “targeted”.

The objective selection of a subpopulation of COPD patients, based on altered or unaltered sputum rheology (now easily quantifiable within minutes), would provide a more effective treatment algorithm than the current standard management. In patients with COPD, asthma, and non-CF bronchiectasis, our team recently demonstrated that sputum rheology (elastic modulus G’, viscous modulus G’’, and critical stress σc), was correlated with MUC5AC and MUC5B mucin content and sputum eosinophilia [25]. We have also shown that sputum rheology can predict sputum eosinophilia at a rate superior or equal to 1.25%, a value that correlated with exacerbations requiring corticosteroids and a reduction in FEV1 in the SPIROMICS cohort [26].

Here, we hypothesize that sputum rheology could guide the prescription of azithromycin in a more appropriate manner than does clinical evaluation, so as to reduce both AECOPD and exposure to antibiotics.

## 2. Materials and Methods

### 2.1. Objectives

#### 2.1.1. Primary Objective

The primary objective of this trial is to compare the exacerbation rates over 12 months between the comparator arm, i.e., a group of COPD patients with frequent exacerbations treated according to clinical evaluation using the Cough and Sputum Questionnaire (CASA-Q; see below for details), and the experimental arm, comprising a similar group in which azithromycin is prescribed according to sputum rheology.

#### 2.1.2. Secondary Objectives

To compare the two arms, we will study:-the exacerbation rates by severity (as observed throughout the study);-the evolution of symptoms, sputum rheology, and lung function (via repeated measurements collected every 3 months);-the medication usage and adverse events (follow-ups for the duration of the study);-the patient trajectories during follow-ups;-the overall clinical improvement achieved by the end of the study and changes in quality of life (via repeated measurements every 3 months); and-the changes in biomarkers of interest (baseline versus end of study).-We will compare the exacerbation rates, throughout the study, of the experimental arm without azithromycin prescription, and of the comparator arm without azithromycin; and between the experimental arm with azithromycin prescription and the comparator arm with azithromycin.-We will evaluate patients in the experimental arm who would have been managed differently using the CASA-Q versus rheology.

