### 2.2. Study Design

COPD CaRhe is a parallel-group randomized trial (36 vs. 36 patients with COPD and frequent exacerbations). It will compare a group of patients treated according to clinical evaluation (and azithromycin will be prescribed according to the Cough and Sputum Assessment Questionnaire (CASA-Q), if patients score < 70) versus a similar group of patients in which azithromycin prescription will be guided by sputum rheology (if the σc > 39). The chosen cut-offs of 70 for the CASA-Q and 39 for the σc correspond to the expected medians of these variables in our population of interest. (See Figure 1).

The CASA-Q is a questionnaire validated in French which aims to rate cough and sputum and their respective impacts on quality of life. According to the national [24] and international [23] recommendations in force, the prescription of azithromycin is conditioned upon the specialist’s free, subjective appreciation of respiratory symptoms, including cough and sputum, in patients with COPD and frequent exacerbations. These symptoms will be assessed here by the CASA-Q [27,28,29,30].

For the variable “critical stress σc”, the threshold of 39 was determined based on a previously published ancillary study [25].

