#### 2.4.1. Comparator Arm

Patients randomized to the comparator arm of the study will receive azithromycin in case of severe sputum symptoms, here defined by a CASA-Q sputum symptom score of <70, so as to homogenize practices between centers. The CASA-Q will be scored every 3 months.

-If the patient presents a sputum symptom score of <70, azithromycin will be initiated for 3 months. This prescription will be renewable every 3 months during the 12 months of follow-up planned in this study if the patient continues to obtain a sputum symptom score of <70.-If the patient has a sputum symptom score of >70, management will not be changed.

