#### 2.4.2. Experimental Arm

Patients randomized to the experimental arm of the study will receive azithromycin according to sputum rheology. Sputum rheology will be quantified every 3 months using a Rheomuco device.

-If sputum has a critical stress σc >39, azithromycin will be initiated for 3 months. This prescription will be renewable every 3 months during the 12 months of follow-up planned in this study.-In the absence of sputum, azithromycin will not be prescribed.

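### The secondary comparisons of arms by azithromycin status are not randomised, because each arm selects its users by a different marker; the resulting bias can go either way

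*Protocol article*

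**What the plan says.** Section 2.1.2 lists, among the secondary objectives, a comparison of exacerbation rates over the whole study "of the experimental arm without azithromycin prescription, and of the comparator arm without azithromycin", and a second one "between the experimental arm with azithromycin prescription and the comparator arm with azithromycin".

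The prescribing rule differs by arm:

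- Comparator arm (2.4.1): "If the patient presents a sputum symptom score of <70, azithromycin will be initiated for 3 months".
- Experimental arm (2.4.2): "Patients randomized to the experimental arm of the study will receive azithromycin according to sputum rheology". Specifically, "If sputum has a critical stress σc >39, azithromycin will be initiated for 3 months", and "In the absence of sputum, azithromycin will not be prescribed".

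In both arms the marker is measured again every 3 months and the prescription can be renewed. Section 2.2 says that the two cut-offs "correspond to the expected medians of these variables in our population of interest". The primary objective (2.1.1) compares the arms as randomised.

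**The concern.** Randomisation balances the two arms as wholes. It does not balance subsets that are picked out by one variable in one arm and by another variable in the other. Users in the comparator arm were selected on symptoms, and users in the experimental arm on rheology; the same holds for non-users. If the two markers carry different information about exacerbation risk, the subsets differ in expected rate before any drug is taken.

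Two features add selection after randomisation:

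- Status is re-decided every 3 months while the comparison runs over the whole study. Membership therefore depends on later symptoms and sputum, which azithromycin may itself change.
- Only the experimental arm moves patients without sputum to the no-azithromycin group. Sputum production is an entry criterion (Table 1), so its later absence is a follow-up event.

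At stake is the interpretation of a secondary result. A low or high rate among the patients whom one rule spares could reflect who was spared and not what the strategy did.

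**Working it through.** **The plan's own figures.** Section 2.14 gives a comparator rate of 3.59/year, SD 2.5, a 50% reduction (difference 1.795), two-sided 0.05 and power 0.80. Then n per group = 2 × (1.960 + 0.842)² × 2.5² / 1.795² ≈ 30.5, so 31 per group and 62 in total, as stated. Dividing 62 by 0.9 gives 69; the plan takes 72, or 36 per arm. The planned randomised comparison reproduces.

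**Size of the subsets.** Cut-offs at the expected medians put about half of each arm on azithromycin: about 18 of 36.

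**Expected ratios with no drug effect.** Assumptions, because the documents give no sizes: σc-high patients have h times the rate of σc-low patients; patients with CASA-Q <70 have c times the rate of the others; effects multiply; markers are independent and cut at the median; status is fixed at baseline.

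- Off azithromycin: the experimental group is all σc-low with mixed CASA-Q, mean (1 + c)/2. The comparator group is all CASA-Q ≥70 with mixed σc, mean (1 + h)/2. Ratio = (1 + c)/(1 + h).
- On azithromycin: experimental mean h(1 + c)/2, comparator mean c(1 + h)/2. Ratio = h(1 + c)/[c(1 + h)].

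With h = 1.5:

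| CASA-Q rate ratio c | Off azithromycin | On azithromycin |
|---|---|---|
| 1.0 | 2.00/2.50 = 0.80 | 3.000/2.500 = 1.20 |
| 1.25 | 2.25/2.50 = 0.90 | 3.375/3.125 = 1.08 |
| 1.5 | 2.50/2.50 = 1.00 | 3.750/3.750 = 1.00 |
| 2.0 | 3.00/2.50 = 1.20 | 4.500/5.000 = 0.90 |

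The true ratio is 1.00 in every row. A drug effect that is the same in everyone multiplies both sides of the on-azithromycin ratio and cancels, so the distortion stays.

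**Correlated markers.** Suppose the underlying (bivariate normal) markers correlate at 0.5. The chance that a patient falls on the same side of both cut-offs is then 1/2 + arcsin(0.5)/π = 2/3. With h = 1.5 and c = 1, the off ratio is 1/(2/3 + 1.5/3) = 0.86 and the on ratio is 1.5/(1.5 × 2/3 + 1/3) = 1.125, both nearer to 1 than 0.80 and 1.20.

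**Error rates.** These come from a simulation of 36 vs 36 patients with 4000 runs per scenario. Counts were negative binomial with mean 3.59, dispersion was set to SD 2.5 before marker effects, status was fixed at baseline, there was no drug effect, markers were independent, and the test was a two-sided t-test at 0.05.

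| h, c | Off: rejections | On: rejections | Whole arms: rejections |
|---|---|---|---|
| 1, 1 | 4.7% | 4.7% | 4.2% |
| 1.5, 1 | 13.2% | 11.9% | 4.8% |
| 1, 1.5 | 13.7% | 13.4% | 5.2% |
| 1.5, 1.5 | 4.9% | 5.3% | 5.1% |

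Whole-arm comparisons hold their level throughout. The simulation does not cover the 3-monthly re-decision of status.

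**The case against.** The article says only that these groups will be compared. It makes no causal or confirmatory claim for them, and the test of the strategy is the whole-arm primary comparison. Asking whether the patients spared by one rule exacerbate less than those spared by the other is a legitimate descriptive question. In the tables above, 0.80 is then a real difference in risk between the spared groups. A label such as exploratory, and the handling of time-varying status, may also stand in an analysis plan that is not shown. All of this stands and limits the weight of the point.

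It does not remove it, because the contrasts as stated cross arms on unlike subsets. The adjustment variables named in 2.5 (prior exacerbations, gender, background treatment, with an open-ended addition) do not name baseline σc or CASA-Q. Stepwise regression (2.14) does not recreate randomised groups. The last item of 2.1.2 looks at patients whom the two markers would manage differently, but only in the experimental arm, so it gives no randomised contrast.

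A reader might infer that these comparisons will favour rheology whenever σc is prognostic. The documents do not support this. The Introduction describes chronic cough and sputum, which the CASA-Q rates, as predictive of exacerbations. Its link from rheology to exacerbations is indirect, through sputum eosinophilia. With equal prognostic strength the bias vanishes; with a stronger CASA-Q it reverses. A reader might also infer that these contrasts are meant to show that rheology safely spares patients azithromycin. The article assigns them no such role.

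**Conclusion.** The two azithromycin-status comparisons in 2.1.2 are non-randomised, and they confound case mix with any effect whenever the two markers differ in prognostic strength. For an assumed σc rate ratio of 1.5 and CASA-Q rate ratios from 1.0 to 2.0, the null value of 1.00 moves to between 0.80 and 1.20 off azithromycin and between 0.90 and 1.20 on it. The direction is unknown, the bias may be nil, and positive correlation between the markers shrinks it. These sizes rest on assumed rate ratios, multiplicative effects, median cut-offs and status fixed at baseline. The primary comparison is not touched. This should be fixed, but it is a matter of one secondary objective and does not threaten the trial's main result.

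**What to change.** Reword the item in 2.1.2 in two parts.

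1. Present exacerbation rates on and off azithromycin descriptively by arm, stated to be non-randomised, with no between-arm test and no causal wording.
2. For the randomised version of the question, compare arms within classes fixed at baseline before randomisation: CASA-Q <70 yes/no by σc >39 yes/no. Focus on the two discordant classes, where the rules lead to different initial prescriptions, and report estimates with confidence intervals.

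The change is one of wording. Section 2.5 names both markers as data required at baseline, and Table 2 schedules sputum rheology and questionnaires at V0 without splitting by arm. The closing sentence of 2.5 places randomisation after entry of one marker or the other, so it is worth confirming that both are entered for every patient first.

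The cost is precision. With uncorrelated markers each class holds about 36/4 = 9 patients per arm. At SD 2.5 the 95% half-width is about 1.96 × 2.5 × √(2/9) = 2.31 exacerbations/year, wider than the planned difference of 1.795. By the same normal approximation, power for that difference is 86% at 36 per arm, 58% at 18, and at 9 about Φ(1.795/1.179 − 1.96) = 33%. With the 0.5 correlation used above, a discordant class falls to 36 × 1/6 = 6 per arm. Hence estimates with intervals, not tests.

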### 2.5. Randomization and Blinding

To optimize the comparability between the two groups, a blocked randomization with randomly selected block sizes will be used to assign patients to treatment groups using a 1:1 allocation ratio. Due to the sample size, stratification will only be performed according to each center. The other variables of interest (e.g., the number of exacerbations in the 12 months prior to inclusion, gender, background treatment, etc.) will serve as adjustment variables in the statistical analysis.

Given the scope of this first study in the field, a level of blinding involving a placebo would not be appropriate. Nevertheless, by blinding the sputum rheology and CASA-Q results for the duration of the study, the blinding allowed by randomization will be ensured. A “guess the arm” question will be asked of investigators and patients at the end of the study to assess the level of blinding.

Data required at the baseline visit, namely sputum rheology and CASA-Q responses, will be promptly entered into the eCRF by a designated person at each center, as these data will condition the allocation of the treatment.

A web-based application within the eCRF (Ennov Clinical) will be created for the purposes of the study and will ensure the randomization of patients. The creation of the eCRF, the sequence, and the allocation modules will be supervised by the Department of Clinical Research and Epidemiology of Montpellier University Hospital. In addition to randomization, the eCRF will also be parameterized to automatically apply the treatment algorithm specific to each study arm. The randomization of patients will be performed by the participating investigators through specific modules in the eCRF. The randomization will be performed after the data entry corresponding to the sputum rheology or the CASA-Q.

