**Assessments**								
Checking Patient’s Logbook: symptoms, exacerbations, unexpected use of drugs or medical resources		✓						
Plethysmography		✓						✓
Spirometry		✓		✓	✓	✓	✓	✓
Questionnaires				✓	✓	✓	✓	✓
Blood Test: blood cell count, CCSP *				✓				✓
Sputum Analysis: rheology, bacteriology		✓		✓	✓	✓	✓	✓
Side Effects			✓	✓				

* CCSP: Club cell secretory protein.

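### Patients whom CASA-Q and rheology would manage differently are evaluated only in the experimental arm, which cannot show whether rheology selects better; the between-arm contrast in these patients should be planned

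*Protocol article*

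**What the plan says.** The hypothesis in the Introduction is that "sputum rheology could guide the prescription of azithromycin in a more appropriate manner than does clinical evaluation". The primary objective (2.1.1) sets the two prescribing rules against each other in everyone randomised: "The primary objective of this trial is to compare the exacerbation rates over 12 months between the comparator arm" and the rheology-guided arm.

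Two secondary objectives in 2.1.2 look at who gets the drug. One compares arms within prescription strata: without azithromycin in each arm, and "between the experimental arm with azithromycin prescription and the comparator arm with azithromycin". The other concerns discordant patients: "We will evaluate patients in the experimental arm who would have been managed differently using the CASA-Q versus rheology". No counterpart is stated for comparator-arm patients whom rheology would have managed differently.

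On the data, section 2.5 says "Data required at the baseline visit, namely sputum rheology and CASA-Q responses, will be promptly entered into the eCRF", and then "The randomization will be performed after the data entry corresponding to the sputum rheology or the CASA-Q". Table 2 lists "Sputum Analysis: rheology, bacteriology" and the questionnaires at V0 and at each follow-up visit, without restriction by arm. Section 2.2 says the two cut-offs "correspond to the expected medians of these variables in our population of interest".

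**The concern.** If both rules indicate azithromycin at V0, or neither does, the patient starts on the same treatment in either arm. The initial difference between the strategies therefore arises only in discordant patients. There, randomisation to arm decides whether azithromycin is started.

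The plan looks at these patients in one arm only. In that arm the rule fixes treatment by type, so treated and untreated discordant patients differ in kind as well as in treatment. The prescription-stratum comparisons do not repair this. The treated stratum is the σc-high group in one arm and the low-CASA-Q group in the other, so the groups compared are not randomised counterparts. Neither objective uses the randomisation to ask in which patients rheology-guided prescribing does better or worse. A reader could take a one-arm result as evidence for or against rheology when it reflects prognosis.

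**Working it through.** **1. The plan's own figure.** Inputs from section 2.14: 3.59/year in the comparator arm, SD 2.5, 50% reduction (Δ = 1.795), two-sided 0.05, power 0.80. n per arm = 2·SD²·(1.96 + 0.84)²/Δ² = 2·6.25·7.849/3.222 = 30.45, so 31 per arm and 62 in total. The stated figure reproduces; the point does not depend on it.

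**2. Treatment at V0 under sections 2.4.1 and 2.4.2.**

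| V0 class | Experimental | Comparator |
|---|---|---|
| σc >39, CASA-Q <70 | azithromycin | azithromycin |
| σc >39, CASA-Q not below 70 (type R) | azithromycin | none |
| σc not above 39, CASA-Q <70 (type C) | none | azithromycin |
| neither | none | none |

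Down the experimental column, type and treatment coincide completely in R and C. Across each of those two rows the comparison is randomised.

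**3. What the one-arm look would return.** Assume a rate ratio of 0.73 in both types (the 27% reduction cited in the Introduction), so that rheology selects no better on relative effect. The ratio of treated to untreated discordants in the experimental arm is 0.73·R/C, where R and C are the untreated rates of the two types (assumed):
- 3.59 and 3.59: 0.73
- 4.5 and 3.0: 3.285/3.0 = 1.095
- 3.0 and 4.5: 2.19/4.5 = 0.49

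The between-arm contrast within each type, treated over untreated, gives 0.73 in all three cases.

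**4. How many patients are discordant.** With both cut-offs at the median and an assumed bivariate normal with latent correlation ρ (not in the document), the discordant share is q = arccos(ρ)/π: 0.50, 0.40 and 0.33 at ρ = 0, 0.3 and 0.5. With 31 analysed per arm that is 15.5, 12.5 and 10.3 discordant patients per arm, and about 8, 6 and 5 per type per arm.

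**5. Dilution.** Assume that the drug works only in σc-high patients (perfect marker), that its average effect is 42% (the larger cited reduction, hence 84% in the σc-high half), and that the V0 decision holds for 12 months. Let λ be the untreated rate.
- Experimental arm: mean reduction 0.5·84% = 42%.
- Comparator arm: both rules positive in (1−q)/2 of patients, so mean reduction 42%·(1−q).
- Difference, all patients: 0.42·q·λ with 31 per arm.
- Difference, discordants: 0.42·λ with 31q per arm.

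The expected z is Δ/(2.5·√(2/n)). Its ratio, discordants to all patients, is 1/√q: 1.41 at ρ = 0 and 1.73 at ρ = 0.5. Two-sided t-test power:

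| ρ | λ = 3.59: all | discordant | λ = 4.54: all | discordant |
|---|---|---|---|---|
| 0 | 0.22 (Δ 0.754) | 0.37 (Δ 1.508) | 0.32 (Δ 0.954) | 0.54 (Δ 1.909) |
| 0.3 | 0.16 | 0.30 | 0.22 | 0.45 |
| 0.5 | 0.12 | 0.26 | 0.17 | 0.38 |

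Two values of λ are shown because section 2.14 gives 3.59 as the comparator-arm rate, and that arm is partly treated. At ρ = 0 the untreated rate would then be 3.59/(1 − 0.42·0.5) = 4.54. Solving again at ρ = 0.5 gives 3.59/(1 − 0.42·0.67) = 4.99, with powers 0.19 and 0.44, so holding 4.54 does not flatter the discordant contrast. With a 27% effect, λ = 3.59 and ρ = 0, the powers are 0.12 and 0.18.

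**6. Precision.** The 95% half-width for the rate difference in discordants is t·2.5·√(2/n): about 1.8 exacerbations/year at 15.5 per arm and 2.3 at 10.3.

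**The case against.** The best defence is that the primary comparison already tests the hypothesis. This stands. It is randomised, contains the discordant patients of both arms, and compares the strategies as they would be used. A reader might infer that the discordant contrast is the only randomised one; the documents do not support that. Nor are comparator-arm data discarded: both markers are scheduled in both arms, and only the analysis is unplanned.

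A reader might also infer that all information about the strategies sits in discordant patients. That holds for the V0 decision only. Prescriptions are reassessed every 3 months, so V0-concordant patients can diverge between arms later and V0-discordant patients can converge. Step 5 ignores this. Describing the gain as equal to doubling the sample size would hold only at ρ = 0 under those static assumptions.

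Section 2.5 could be read as contradicting itself on data entry. The arm is unknown before randomisation and both results are described as required, so the sensible reading is that both are entered; the *or* needs clarifying and is no proof of a flaw.

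Finally, an analysis plan that is not shown could add the contrast, and the objective may be meant only as a description of reclassification. A count of reclassified patients is legitimate in one arm. But the article fixes the analysis set as one arm, and outcomes in that set cannot bear on selection.

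**Conclusion.** The point holds in limited form. The stated evaluation of discordant patients cannot separate azithromycin effect from patient type, and the neighbouring prescription-stratum comparisons do not make up for it. A randomised contrast by V0 class is available from data already planned. It is less diluted than the primary comparison and shows in which type of patient a difference arises.

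The gain in expected z is a factor of 1.41 to 1.73 for ρ from 0 to 0.5. It rests on a perfect marker, median cut-offs and the V0 decision held for a year, none of which the document establishes. Even then discordant power reaches only 0.54, so this is supportive estimation. With about 5 to 8 patients per type per arm, a formal arm-by-type interaction test would be close to uninformative. The validity of the primary analysis is unaffected.

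**What to change.** - In 2.1.2, replace the restriction to the experimental arm with both arms, classified by V0 CASA-Q <70 and V0 σc >39.
- Pre-specify, as a supportive analysis, the experimental-to-comparator exacerbation rate ratio in V0-discordant patients: overall, and descriptively for each of the two discordant types, with confidence intervals and no firm interaction test.
- Use the V0 class only, because later classes can be affected by treatment.
- In 2.5, state that both results (*and*, not *or*) are entered before randomisation, backed by an eCRF check.
- Keep the all-randomised comparison primary.

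The cost is some analysis wording and one eCRF check, with no new measurements. The downside is small cells and wide intervals, which the report should state plainly.
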